### **9.3. Collecting, Recording and Reporting of Serious Adverse Events (SAEs) to the Health Science Authority (HSA)**

All SAEs that are unexpected and related to the study drug must be reported to HSA.

“A serious adverse event or serious adverse drug reaction is any untoward medical occurrence at any dose that:

- Results in death.
- Is life-threatening (immediate risk of death).
- Requires inpatient hospitalization or prolongation of existing hospitalization.
- Results in persistent or significant disability/incapacity.
- Results in congenital anomaly/birth defect.
- Is a Medically important event.

Medical and scientific judgment should be exercised in determining whether an event is an important medical event. An important medical event may not be immediately life threatening and/or result in death or hospitalization. However, if it is determined that the event may jeopardize the subject and/or may require intervention to prevent one of the other AE outcomes, the important medical event should be reported as serious.”

All SAEs that are unexpected and related to the study drug will be reported. The investigator is responsible for informing HSA no later than 15 calendar days after first knowledge that the case qualifies for expedited reporting. Follow-up information will be actively sought and submitted as it becomes available. For fatal or life-threatening cases, HSA will be notified as soon as possible but no later than 7 calendar days after first knowledge that a case qualifies, followed by a complete report within 8 additional calendar days.

### **9.4. Safety Monitoring Plan**

An independent DSMB will be established to monitor the study during Phase A-C of the study (first booster). The DSMB will evaluate the study design and protocol, and review the accumulative data of safety and immunogenicity, as well as subject enrolment, protocol deviations, and data quality. The DSMB will meet after 10 participants in each intervention group have completed assessments at study day 28. Since participant recruitment may start at different time points for intervention groups 1 to 4 depending on availability of the vaccines, separate DSMB meetings may be needed for data review.

A DSMB Charter will be drawn up, which describes the scope of data to be reviewed, memberships of DSMB, terms of reference, decision-making process, and timing and frequency of interim analyses (with specification of stopping guidelines if any). An interim analysis report will be prepared for each DSMB data review, which will include summary data on participant enrolment, data quality, demographic and baseline characteristics, protocol deviation, safety data, and immunogenicity data. Following review of interim data, DSMB may recommend discontinuation of participant enrolment to a study arm on the basis of safety concern and/or

futility in immunogenicity compared with the control arm. The DSMB may request additional data review if necessary.

For Phase D of the study involving vaccines which have been authorised for use in Singapore by the HSA, study safety will be monitored by the PI. This will include monitoring rates of COVID-19 infections and SAEs between study groups.

## **9.5. Complaint Handling**

The contact information of the PI and DSRB will be provided to all study participants, which is available in the Participant Information and Informed Consent Sheet.

## **10. DATA ANALYSIS**

### **10.1. Data Quality Assurance**

Study monitors must be allowed to visit the study site periodically to assess the data quality and study integrity. Study monitors will review the study records on site to directly compare them with source documents, discuss the conduct of the study with the Investigator, and verify that the facilities remain acceptable. Such visits will be scheduled in advance to allow arrangements of diaries and personnel as appropriate. In addition, the study may be evaluated by government inspectors who must be allowed access to CRFs, source documents and other study files.

### **10.2. Data Entry and Storage**

A clinical database will be developed and validated to collect all clinical and laboratory related information. The database will include information on demographics, medical history, vaccine arm allocation, vital signs, and laboratory investigation tests. The study team will manage the data and will conduct quality control of the data following their own standard operating procedures.

## **11. SAMPLE SIZE AND STATISTICAL METHODS**

### **11.1. Determination of Sample Size**

Based on the data from our ongoing COVID-19 vaccine immune-monitoring study (SCOPE), the mean level of SARS-CoV-2 anti-spike immunoglobulins was 84% (SD=15%) at 28 days after the second dose. This was determined using a SARS-CoV-2 surrogate virus neutralisation test (sVNT) that detects total immuno-dominant neutralising antibodies targeting the viral spike (S) protein receptor-binding domain in an isotype- and species-independent manner. We expect immunogenicity will be boosted back to the same level after the booster dose in the control arm. With an assumed immunogenicity level of 81% in an intervention arm and a non-inferiority margin of -10%, a sample size of 87 subjects per arm will ensure concluding non-inferiority of the intervention arm against the control arm with 80% power. The sample size is calculated at a one-sided 2.5% significance level and allows for a 15% dropouts. A sample size will offer power of 85.1% based on the above parameters.

Since recruitment of subjects to intervention arms may be activated in a staggered way depending on availability of the vaccines, and recruitment to the control arm will continue until the target

sample size of 100 is achieved in each intervention arm, we prepare to enrol a double sample size in the control arm for the purpose of study planning. This gives a total sample size of up to 600 subjects.

For Phase D of the study, the objective is to estimate the mean difference in humoral immunity (log10-transformed anti-S at day 28) between Pfizer vs Moderna, Pfizer vs Nuvaxovid and Moderna vs Nuvaxovid received as 2nd booster (three mean difference estimations). No hypothesis testing will be performed.

The standard deviation of day 28 log10-transformed anti-S titre from Phase A of the study was assumed to apply to responses to the second booster (note data from those aged 60 years and above per current MOH advisory for a second COVID-19 booster). Using confidence interval approach for sample size calculation, a sample size of 50 per arm (after allowing 5% dropout rate) was estimated to produce two-sided 95% confidence interval with distance from difference in means to limits that is equal to 0.13 when standard deviation of log10-transformed anti-S titre is assumed to be 0.32 for both arms that is being compared.

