Since the first detection of the XBB Omicron subvariant in August 2022 in India, it has been detected in more than 17 countries to-date including Singapore, Australia, Bangladesh, Denmark, Japan and the US. The current wave of COVID-19 cases in Singapore, driven by the XBB strain, is expected to peak in mid-November 2022 with about 15,000 daily cases on average. The proportion of reinfections among total COVID-19 cases in Singapore is also on the rise, currently making up about 17% of total new cases. To combat the rising COVID-19 infections and reinfections, the bivalent Moderna/Spikevax vaccine was added to the National Vaccination Programme from 14 October 2022 for persons who have yet to achieve minimum protection (i.e. received at least 3 doses of mRNA/Nuvaxovid or 4 doses of Sinovac-Coronavac), or those aged 50 years and above who have received their last vaccine dose more than five months ago. On 25 October 2022, Singapore's HSA granted interim authorisation of a booster dose of the Pfizer-BioNTech bivalent vaccine for individuals aged 12 years and older.

From 14 Nov 2022, a second booster dose from five months to one year after the last vaccine dose is recommended by MOH for all individuals aged 18 years or older.

The updated bivalent vaccine is preferred for this. A person is considered up-to-date with their COVID-19 vaccination if they have received at least the minimum protection and their last vaccine dose was received within the past one year. The bivalent Moderna/Spikevax vaccine is currently available, and the bivalent Pfizer-BioNTech vaccine is expected to be available by the end of this year.

PRIBIVAC will assess a heterologous prime-boost-boost strategy in comparison with a homologous regimen in order to compare short and long-term immunogenicity of different COVID-19 vaccine combinations against the ancestral SARS-CoV-2 as well as different VOCs. Initial phases of the study have studied homologous versus heterologous vaccines at the first booster, later phases will study these as the second booster.

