### **3.4. Exclusion Criteria**

1. Known history of SARS-CoV-2 or SARS-CoV-1 infection;
2. Previously received an investigational coronavirus vaccine;
3. Previously received a SARS-CoV-2 monoclonal antibody;
4. Current or planned simultaneous participation in another interventional study;
5. A history of anaphylaxis, urticaria, or other significant adverse reaction requiring medical intervention after receipt of a COVID-19 vaccine, or otherwise have a contraindication to one of the available study vaccines per the approved label;
6. Individuals who are immunocompromised (e.g. active leukaemia or lymphoma, generalised malignancy, aplastic anaemia, solid organ transplant, bone marrow transplant, current radiation therapy congenital immunodeficiency, HIV/AIDS with CD4 lymphocyte count  $< 200$  and patients on immunosuppressant medications);
7. Received systemic immunosuppressants or immune-modifying drugs for  $>14$  days in total within 6 months prior to Screening (for corticosteroids  $\geq 20$  milligram per day of prednisone equivalent). Topical tacrolimus is allowed if not used within 14 days prior to Day 1;
8. Individuals who are pregnant or breast feeding;
9. Chronic illness that, in the opinion of the study team, is at a stage where it might interfere with trial conduct or completion;
10. Deprived of freedom by an administrative or court order, or in an emergency setting, or hospitalised involuntarily;
11. Current alcohol abuse or drug addiction that might interfere with the ability to comply with trial procedures in the opinion of the study team;
12. Moderate or severe acute illness/infection (according to study team's judgement) on the day of vaccination, or febrile illness (temperature  $\geq 37.5^{\circ}\text{C}$ ). A prospective participant should not be included in the study until the condition has resolved or the febrile event has subsided.

For Phase D of the trial exclusion criteria 1 and 4 will no longer apply: exclusion criteria 1 is no longer relevant as it not a consideration in MOH recommendations for COVID-19 booster vaccination, and exclusion criteria 4 because of the broad recommendations from MOH for keeping up to date with COVID-19 boosters.

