### *c. Efficacy Analyses*

Graphical plots will be produced for the various immunity endpoints to depict the change of immunity levels over time. Levels of SARS-CoV-2 anti-spike immunoglobulins will be summarized by study arm and by randomisation stratification factors. Mean difference and its 95% CI in levels of SARS-CoV-2 anti-spike immunoglobulins between an intervention arm and the control arm (for Phase A-C), and between pairwise arms (for Phase D) will be estimated from a general linear regression model which adjusts for level of SARS-CoV-2 anti-spike immunoglobulins at baseline, and randomisation stratification factors. If the lower bound of the 95% CI of Phase A-C SARS-CoV-2 anti-spike immunoglobulins falls above -10% (the pre-specified non-inferiority margin), non-inferiority of the intervention arm will be concluded. For Phase D, reported mean differences and 95% CIs are exploratory in nature. Analysis of repeated measurements of immunity endpoints will be performed with the use of mixed effects models that adjust for baseline values and randomisation stratification factors. Log-transformation of the data may be applied as needed before the analyses.

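### Phase D's half-width of 0.13 rests on an SD from Phase A participants aged 60 and over with no known infection, a narrower group than Phase D enrols, and has no reserve at 50 per arm

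*Protocol*

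**What the plan says.** Section 11.1 gives Phase D an estimation objective: three pairwise mean differences in log10 anti-S at day 28, with no hypothesis test. The sample size is "a sample size of 50 per arm (after allowing 5% dropout rate", chosen to give a "two-sided 95% confidence interval with distance from difference in means to limits that is equal to 0.13". The "standard deviation of log10-transformed anti-S titre is assumed to be 0.32 for both arms", and the SD of the "titre from Phase A of the study was assumed to apply to responses to the second booster". A parenthesis gives the source: "note data from those aged 60 years and above per current MOH advisory for a second COVID-19 booster".

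Other sections describe a wider Phase D population:

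- **Age.** Section 1.2 a says that from 14 November 2022 a second booster "is recommended by MOH for all individuals aged 18 years or older". Section 3.3 ties Phase D enrolment to the MOH recommendation and leaves the minimum age at 21. Section 6.1 stratifies Phase D at below 60 against 60 and over.
- **Infection.** Exclusion criterion 1 in section 3.4 is a known history of SARS-CoV-2 or SARS-CoV-1 infection, and it applied in Phase A. The same section then says: "For Phase D of the trial exclusion criteria 1 and 4 will no longer apply". Section 1.2 c describes infection in the Omicron wave as highly prevalent but gives no figure.
- **Number.** Section 3.1 enrols 250 in Phase D; section 5.1 allocates equally to three vaccines.

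Section 11.2 c specifies a linear model "which adjusts for level of SARS-CoV-2 anti-spike immunoglobulins at baseline, and randomisation stratification factors". In Phase D the stratification factors are age group, primary series and first booster vaccine. Time since the last dose was a stratum for the first booster but is not one for the second.

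**The concern.** Phase D has no test and no power statement, so the 0.13 half-width is its only quantitative justification. It depends directly on the SD, and the stated reason for taking the SD from those aged 60 and over is an advisory that the protocol itself reports as widened.

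The source group also differs from Phase D in infection history. A mixture of previously infected and uninfected participants will have a larger overall spread than either group alone if their mean titres differ and the spread within each is unchanged. There is a product difference too: Phase A used mRNA boosters, whereas Phase D adds Nuvaxovid and lets an mRNA arm contain both bivalent and monovalent vaccine, depending on stock. The protocol gives neither an argument for carrying 0.32 over nor a sensitivity range. If the true SD is larger, the pairwise differences will be less precise than the design promises.

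**Working it through.** **Inputs.** From section 11.1: SD 0.32 in each arm, half-width 0.13, two-sided 95%, 50 enrolled per arm, 5% dropout. From sections 3.1 and 5.1: 250 over three equal arms, so 250/3 ≈ 83 per arm. Evaluable numbers, rounded down: 50 × 0.95 = 47.5, so 47; 83 × 0.95 = 78.85, so 78.

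**Formula.** Half-width w = 1.96 × SD × √(2/n), with n evaluable per arm and no covariate adjustment.

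**The plan's own figure.** n = 2 × (1.96 × 0.32 / 0.13)² = 46.6, so 47; 47/0.95 = 49.5, so 50 enrolled. At n = 47, w = 1.96 × 0.32 × √(2/47) = 0.129, or 0.131 with the t quantile. The stated 0.13 at 50 per arm is reproduced.

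**Largest SD that keeps 0.13.** SD = 0.13 / (1.96 × √(2/n)): 0.32 at n = 47, and 0.41 at n = 78.

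**Sensitivity.** The protocol gives no SD for the Phase D population, so the values above 0.32 are assumptions.

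| SD | w, 50 enrolled (n = 47) | w, 83 enrolled (n = 78) | Enrolled per arm for 0.13 |
|---|---|---|---|
| 0.32 | 0.129 | 0.100 | 50 |
| 0.35 | 0.142 | 0.110 | 59 |
| 0.40 | 0.162 | 0.126 | 77 |
| 0.45 | 0.182 | 0.141 | 98 |
| 0.50 | 0.202 | 0.157 | 120 |

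As a ratio of geometric means, 0.13 is a factor of 10^0.13 = 1.35 either side of the estimate; 0.16 is 1.45 and 0.20 is 1.58.

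**What prior infection alone could add.** Assume a within-group SD of 0.32, a proportion p previously infected and a difference d in mean log10 titre. The total SD is √(0.32² + p(1 − p)d²). With p = 0.5:

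- d = 0.1: SD 0.324, w = 0.131 (n = 47) or 0.102 (n = 78)
- d = 0.3: SD 0.353, w = 0.143 or 0.111
- d = 0.5: SD 0.406, w = 0.164 or 0.127

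**What the planned adjustment could recover.** If the covariates have correlation ρ with the day-28 titre, the residual SD is SD × √(1 − ρ²). To hold 0.13 at n = 47, ρ must be about 0.59 for SD 0.40 and 0.77 for SD 0.50. At n = 78 no adjustment is needed for SD 0.40, and ρ of about 0.56 is needed for SD 0.50. The protocol reports no such correlation.

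**The case against.** The sponsor has several fair answers.

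- **The arithmetic is right.** A reader might infer that 0.13 is a miscalculation. It is not; it follows from the stated inputs.
- **No larger SD is documented.** A reader might infer that the Phase D SD is known to exceed 0.32. Nothing in the protocol shows this. For age, section 1.2 a reports lower titres in older people, which says nothing about their spread. For infection, the direction is plausible, but prevalence and titre difference are not given. This objection stands, and the result has to be a range.
- **Section 3.1 plans more than 50 per arm.** With 250 in total, every mixture shown above stays below 0.13. This also stands, but section 11.1 never uses 250; it justifies 50 per arm, or 150 over three arms.
- **The model already adjusts for baseline anti-spike level and age group.** Baseline level is a partial proxy for both infection and waning, so the unadjusted widths are probably somewhat pessimistic. By how much is unknown.
- **Omitting prior infection is not a source of bias.** A reader might infer that the pairwise differences would be confounded. Allocation is randomised, so leaving the term out costs at most precision. Further covariates could also be set in an SAP that is not at hand.
- **Phase A was not shown to be infection-naive.** The exclusion covers known history only, and no serological exclusion is stated. The contrast with Phase D is in known infection.

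None of this supports the reason that section 11.1 gives for using an SD from those aged 60 and over.

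**Conclusion.** The concern holds as a weakness in the planning basis. The protocol carries 0.32 from Phase A participants aged 60 and over, without known infection, to a Phase D population open from age 21 and to the previously infected, on the strength of an advisory that its own section 1.2 a supersedes. At 50 per arm the half-width has no reserve: 0.16 at SD 0.40 and 0.20 at SD 0.50, unadjusted. At about 83 per arm, 0.13 survives up to an SD of about 0.41. These widths rest on assumed SDs, equal spread in both arms, 5% dropout and no gain from covariates.

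Severity is minor. Section 11.2 c calls the Phase D estimates exploratory, and the reported intervals will reflect the observed variance, so a wrong planning SD would make the stated precision misleading without invalidating a conclusion.

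**What to change.** In section 11.1:

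1. Remove the note on those aged 60 and over, which no longer agrees with sections 1.2 a and 3.3.
2. Reconcile 50 per arm with the 250 in section 3.1, and base the precision statement on the resulting number.
3. Re-derive the SD from Phase A participants of all ages. These data come from people without known infection and cannot supply infection-related variance, so also state the half-width over SD 0.32 to 0.50 at the reconciled number.

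In section 11.2 c, add known prior infection and time since the last vaccine dose as Phase D covariates alongside baseline anti-spike level, and say that the purpose is precision. Medical history and the Visit 1 infection review should supply the first; the five-month eligibility check should supply the second.

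The cost is a short recalculation from data already held, two model terms needing no new data collection, and possibly a less favourable stated half-width. If the reconciled number is 250, enrolment need not rise to keep 0.13 at SD 0.40, since 3 × 77 = 231.

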## **11.2. Statistical and Analytical Plans**

### *a. General Considerations*

The safety analysis set consists of all participants who received the study vaccine. The efficacy analysis set is defined as all participants who are assessable with respect to immunogenicity after receiving the study vaccine. The analysis will include all study arms, including those in which participant enrolment is discontinued following interim analysis. Separate set of analyses will be done for Phase A-C and Phase D.

### *b. Safety Analyses*

Data of AEs, SAEs, Grade 3 and 4 clinical or laboratory AEs will be summarised by study arm with frequency and proportion of participants having the event, as well as the number of events. For SAEs and Grade 3 and 4 AEs, the proportion of participants with the events will be provided together with its 95% confidence interval (CI).

### *c. Efficacy Analyses*

Graphical plots will be produced for the various immunity endpoints to depict the change of immunity levels over time. Levels of SARS-CoV-2 anti-spike immunoglobulins will be summarized by study arm and by randomisation stratification factors. Mean difference and its 95% CI in levels of SARS-CoV-2 anti-spike immunoglobulins between an intervention arm and the control arm (for Phase A-C), and between pairwise arms (for Phase D) will be estimated from a general linear regression model which adjusts for level of SARS-CoV-2 anti-spike immunoglobulins at baseline, and randomisation stratification factors. If the lower bound of the 95% CI of Phase A-C SARS-CoV-2 anti-spike immunoglobulins falls above -10% (the pre-specified non-inferiority margin), non-inferiority of the intervention arm will be concluded. For Phase D, reported mean differences and 95% CIs are exploratory in nature. Analysis of repeated measurements of immunity endpoints will be performed with the use of mixed effects models that adjust for baseline values and randomisation stratification factors. Log-transformation of the data may be applied as needed before the analyses.

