#### **d. Rationale for Study Design**

PRIBIVAC is an adaptive, randomised, subject-blinded, controlled trial to assess the immunogenicity and safety of heterologous boost COVID-19 vaccine regimens compared with a homologous boost regimen. Potential participants would have already received a primary vaccine series with BNT162b2 or mRNA-1273 prior to randomisation.

In Phases A-C of this study, the booster vaccine for the control group was the homologous mRNA vaccine (e.g. BNT162b2 + BNT162b2 or mRNA-1273 + mRNA-1273), while the heterologous vaccine candidates were an alternative COVID-19 vaccine. For individuals randomised to intervention group 1 the mRNA booster vaccine administered was heterologous to the primary series (e.g. BNT162b2 + mRNA-1273 or mRNA-1273 + BNT162b2), while for other intervention groups this included vaccines of alternate designs:

- Control group: Homologous mRNA booster vaccine
- Intervention group 1: Heterologous mRNA booster vaccine (Phase A)
- Intervention group 2: COVAXIN® (Phase B)
- Intervention group 3: Nuvaxovid (Phase C)

Vaccine candidates in phases A-C entered the study at different time points and participants were randomised at equal probability to the available intervention arms at the time of randomisation. This will reduce the risk of bias (e.g. participant preference for a certain arm) compared with a non-randomised design. While an ideal scenario is to have all the selected vaccines approved prior to the start of recruitment, due to the unknown time of availability of vaccine candidates A, B and C, and the urgency of the current situation, recruitment to the control and intervention group 1 (Phase A) was initiated from 12 Oct 2021. Intervention group 2 (Phase B) was added in January 2022 and discontinued 15 March 2022 per the recommendation from the Data Safety Monitoring Board, who reviewed the trial's preliminary results from the first 10 COVAXIN recipients up to Day 28 post-booster. Recruitment to Intervention group 3 (Phase C) was terminated prior to initiation due to delays in the availability of Nuvaxovid which despite receiving interim authorisation by HSA in February 2022 has only become available for administration in late May 2022.

As of 18-May-2022 uptake of the first booster has increased to 75% of the population – with a sharp increase in uptake from January 2022 following governmental policy changes to the definitions of vaccinated status. A significant proportion of those who have not taken their

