## **6. METHODS AND ASSESSMENTS**

### **6.1. Randomisation and Blinding**

Randomisation will be performed using a web-based randomisation system hosted by Singapore Clinical Research Institute (SCRI), in which a randomisation list with randomised permuted blocks will be generated by the trial statistician. Password secured accounts will be assigned to the site personnel who are responsible for the randomisation, where he/she can log into the randomisation system using the Internet.

For the first booster part of the trial randomisation will be stratified by the following criteria:

1. Age (<60, ≥60)
2. Primary vaccine series (BNT162b2 or mRNA-1273)
3. Time from 2nd vaccine dose administered (6-9 months, >9 months)

For the second booster part of the trial randomisation will be stratified by the following criteria:

1. Age (<60, ≥60)
2. Primary vaccine series (BNT162b2 or mRNA-1273)
3. First booster vaccine received (BNT162b2 or mRNA-1273)

Eligible participants will be randomised in equal proportions to each of the study arms that are open for randomisation. Enrolment to a study arm will be discontinued if recommended by DSMB or if the target sample size of 100 in the study arm has been reached. In the scenario where recruitment is discontinued in any of the intervention arms from 1 to 4 at the interim analysis, randomisation to the control arm may continue beyond 100 participants until the target sample size of 100 participants has been reached in the remaining intervention arms.

Allocation concealment will be maintained until the registration and randomisation process have been completed. For Phase A-D of the study, vaccine allocation will be single-blind, i.e. only participants will be blinded. Blinding will be maintained for the participants till their Day-28 Visits (Visit 3).

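### As written, the Phase A-C analysis compares COVAXIN (open January to 15 March 2022) with controls recruited from 12 October 2021, with no term for recruitment period

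*Protocol*

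**What the plan says.** Section 11.2 c fixes the comparator and the covariates of the primary Phase A-C analysis. The mean difference is taken "between an intervention arm and the control arm (for Phase A-C"), from a linear model "which adjusts for level of SARS-CoV-2 anti-spike immunoglobulins at baseline, and randomisation stratification factors". Non-inferiority is concluded if the lower 95% confidence limit lies above -10%.

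Section 6.1 introduces the stratification factors with "For the first booster part of the trial randomisation will be stratified by the following criteria" and lists age, primary vaccine series and time from the second dose. None is a calendar or phase term.

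Section 11.2 a adds "Separate set of analyses will be done for Phase A-C and Phase D", so Phases A, B and C form one analysis set. It also states: "The analysis will include all study arms, including those in which participant enrolment is discontinued following interim analysis". COVAXIN therefore stays in the analysis although its enrolment was stopped.

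Section 1.2 d gives the dates: "recruitment to the control and intervention group 1 (Phase A) was initiated from 12 Oct 2021", and "Intervention group 2 (Phase B) was added in January 2022 and discontinued 15 March 2022". It also says that participants were randomised with equal probability among the arms available at the time. Sections 6.1 and 11.1 plan one control arm that recruits throughout. Under 6.1, if an arm is stopped, "randomisation to the control arm may continue beyond 100 participants until the target sample size of 100 participants has been reached" in the remaining arms.

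**The concern.** A participant randomised to control between 12 October and December 2021 had no chance of receiving COVAXIN. Pooling such controls with those of January to March 2022 gives a COVAXIN contrast that is randomised in part and a comparison across calendar time in part. Section 1.2 d justifies randomisation as a protection against bias compared with a non-randomised design; the pooled contrast partly gives that up.

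The protocol itself records relevant changes over these months. Section 1.2 a describes the emergence of Omicron in November 2021 and a booster requirement for keeping vaccinated status. Section 1.2 d describes a sharp rise in booster uptake from January 2022, and expects many of those still without a booster to have had COVID-19 in the Omicron wave. The people available for a first-booster trial were therefore changing.

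At stake is whether the COVAXIN estimate, and any non-inferiority statement based on it, reflects the vaccine or partly the period of recruitment.

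**Working it through.** **1. Which contrasts are affected.**
- Group 1 opened together with control on 12 October 2021, with equal allocation. Not affected.
- COVAXIN opened in January 2022 and stopped on 15 March 2022. Controls randomised in October to December 2021 are non-concurrent; those of January to March 2022 are concurrent. Partly affected.
- Nuvaxovid in Phase C was terminated before any recruitment. No contrast arises.

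**2. What the covariates remove.** Baseline anti-spike level and time from second dose absorb part of any drift. They do not absorb infection between Day 0 and Day 28, or changes in who was still unboosted. Exclusion criterion 1 (section 3.4) covers only known past infection, and the efficacy set in 11.2 a does not remove participants infected after vaccination.

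**3. The plan's own sample size** (section 11.1: means 84% and 81%, SD 15, margin -10, one-sided 2.5%, 80% power, 15% dropout). The distance from the assumed difference to the margin is 10 - 3 = 7 points.
- Normal formula: n = 2 × (15 × (1.960 + 0.842) / 7)² = 72.1, so 73 per arm; 73 / 0.85 = 85.9, so 86.
- With the t distribution: 74 per arm; 74 / 0.85 = 87.06, which matches the stated 87.
- The sentence giving 85.1% power omits its sample size. Assuming the target of 100 per arm, 85 are evaluable, and power is 86.0% (normal) or 85.7% (t), close to the stated figure.

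Both stated figures follow from a 1:1 comparison, so neither depends on the doubled control arm.

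**4. Size of the bias.** Let f be the share of controls that is non-concurrent and D the drift in Day-28 level, in percentage points, left after adjustment. Then bias = f × D. The protocol gives neither, so f = 0.5 and D = 2 or 5 are assumptions.

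Planned design: 100 versus 200 with 15% dropout gives 85 versus 170 evaluable. SE = 15 × √(1/85 + 1/170) = 1.99 points.
- No bias: false non-inferiority at a true difference of -10 is 2.5%; power at -3 is 94%.
- D = 2 (bias 1 point), favouring the intervention: false non-inferiority = 1 - Φ(1.960 - 1/1.99) = 7.2%. Against it: power at -3 = Φ((7 - 1)/1.99 - 1.960) = 85%.
- D = 5 (bias 2.5 points), favouring it: 1 - Φ(1.960 - 2.5/1.99) = 24%. Against it: power = Φ((7 - 2.5)/1.99 - 1.960) = 62%.

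**5. COVAXIN at a plausible realised size.** The protocol mentions the first 10 recipients and gives no final number. Section 3.1 gives 150 enrolled across Phases A to C; with equal allocation between control and group 1, control is about 75 at most. Assume 10 to 20 COVAXIN recipients and 50 to 70 pooled controls.
- Power at -3 with concurrent controls: 17% (10 versus 10) to 30% (20 versus 20).
- With pooled controls: 26% (10 versus 50) to 44% (20 versus 70).
- False non-inferiority at 10 versus 50, SE = 15 × √(1/10 + 1/50) = 5.20: 3.9% for a 1-point bias and 7.0% for a 2.5-point bias.

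**6. Price of restricting to concurrent controls.** √(1/20 + 1/20) = 0.316 against √(1/20 + 1/70) = 0.254, a ratio of about 1.25. In the planned design, 85 versus 85 keeps 85.7% power, against 93.8% for 85 versus 170 (both t).

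**The case against.** The strongest reply is that the protocol says only the control arm and never states that non-concurrent controls are pooled; a statistical analysis plan, which was not available for this review, could define the comparator for each contrast. That weakens the point but does not remove it. The protocol names one control group, one Phase A-C analysis set and a specific list of covariates, and an analyst who followed it would pool.

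A second reply is that one discontinued, small arm carries little inferential weight. That stands, and it limits the importance of the point.

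Four stronger readings are tempting, and the protocol does not support them:
- A reader might infer that every Phase A-C comparison is affected. Group 1 opened with control, and Phase C did not recruit.
- A reader might infer a bias towards non-inferiority, because undetected Omicron infection would raise later titres. Known infection was excluded and baseline level is adjusted for. The selection of late boosters could act either way, so the direction is unknown.
- A reader might add assay batch drift or controls recruited after 15 March 2022. The assay descriptions in 6.3 say nothing about batches or timing. Section 6.1 permits continued control recruitment, but the protocol does not document any after that date.
- A reader might size the bias in log10 titre. The margin is -10 on a percentage scale and log-transformation is optional in 11.2 c, so such a figure could not be set against the decision rule.

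**Conclusion.** The concern holds for COVAXIN alone. Section 11.2 c, read with 11.2 a, 6.1 and 1.2 d, yields a partly non-randomised contrast with no adjustment for recruitment period. The direction of bias is unknown, and its size cannot be derived from the protocol. The rise in false non-inferiority from 2.5% to about 7% or 24% is an illustration for the planned arm sizes. It rests on an assumed half of controls being non-concurrent and an assumed 2-point or 5-point residual drift. At the assumed realised sizes, biases of 1 to 2.5 points have a smaller effect (3.9% to 7.0%), and the arm probably cannot establish non-inferiority under either choice of controls. The stated 87 per arm and 85.1% power are not in dispute. This is a cheap improvement to the analysis wording. It does not call the group 1 result into question.

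**What to change.** In section 11.2 c, state that COVAXIN is compared only with controls randomised while the COVAXIN arm was open. Report the pooled-control result, with a randomisation-period term in the model, as a sensitivity analysis.

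The change is one or two sentences and needs only the randomisation dates. The downside is a wider COVAXIN interval, with an SE about 25% larger if the comparison is 20 versus 20 rather than 20 versus 70 (assumed sizes). The sample size and power in 11.1 need no change because they are already based on a 1:1 comparison.
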